### Trial Intervention

#### tACS

This trial uses a Soterix Medical 1×1 Mini-CT tES Stimulator, licensed for use in Canada. It is a small and portable device, with 3 rechargeable 800 mAh batteries and the necessary accessories and calibration to begin tACS right out of the box. The device does not allow initiation of stimulation if the contact quality is outside the desired range. If the session is already underway, the device will alert the user with continuous beeping to prompt immediate corrective action. Stimulation is also recorded by the device, which provides a detailed log of the stimulation session, including pause events, critical events such as poor contact quality, and the total time of the session. Frequency has a 1 Hz resolution and can be adjusted from 1 to 200 Hz. Current intensity has a 0.01 mA resolution and can range from +0.10 to 4.00 mA. Session duration and ramp duration are also adjustable, with session times ranging from 5 to 60 minutes and ramp times from 10 to 30 seconds. The electronic unit is intended to generate the electrical pulses of a specified waveform, duration, and repetition rate. The pulses are delivered to a patient via stimulating electrodes positioned at the patient’s head according to the required technique. The mini-CT is European Union Conformity marked. The SNAP Headset can be used to position Soterix Medical SNAP pads at designated transcranial direct current stimulation and transcranial electric stimulation locations, maximizing reproducibility and participant comfort. The custom headgear with fixed electrode sites and a universal, one-size-fits-all design makes for a simplistic setup for 1×1 stimulation.

#### CBTp

The intervention consists of 16 individual-based weekly sessions, with follow-up assessments (1 month and 3 months after the intervention). The trial intervention is summarized in Table 1.

**Table 1 table1:** Trial intervention.

Arms	Assigned intervention
Experimental: tACS^a^/CBTp^b^ (both active)	tACS: gamma band electric stimulation for 20 minutes at the beginning of each CBTp session. After 20 minutes, the device remains in place, but the electric stimulation will be automatically stopped. The CBTp will continue up to a total of 50 minutes/session. CBTp: 16 individual-based, weekly sessions each of 50 minutes in duration and 2× booster sessions at months 1 and 3 after intervention.
Sham comparator: sham tACS/CBTp (only CBTp active)	For the sham group, the investigators will use the same tES^c^ device; the sham stimulation will be applied only for a few seconds in the sham group. The CBTp will follow the same protocol for both arms.

^a^tACS: transcranial alternating current stimulation.

^b^CBTp: cognitive behavioral therapy for psychosis.

^c^tES: transcranial electric stimulation.

### Concomitant Medications/Interventions

#### Permitted/Supportive

Participants will be on their usual medication regimen, with no significant changes for at least 1 month (preferably 3 months) before enrollment. Small, symptomatic medication changes are permitted at the principal investigator’s judgment. These changes should not interfere with the assessments. For example, the use of benzodiazepines will be on hold from midnight of the day before the evaluations. Aside from antipsychotic medication, any pharmacological products are permitted as long as they are part of the usual medication regimen of the participant. Minor adjustments or symptom-treating medication (eg, insomnia and anxiety) are permitted at the principal investigator’s best judgment, provided they do not interfere with project activities.

Other interventions are permitted, but only if they are continuous and started 3 months before enrollment. For example, the participants would not be allowed to start a keto diet during the study, but they will be allowed to follow that diet if they started at least 3 months before enrollment, and it will be ongoing until the end of the study.

#### Not Permitted Concomitant Medications/Interventions

Participants must withhold benzodiazepines and other medications for sleep or anxiety for at least 8 hours before assessments, avoid using illicit drugs during research activities, refrain from hormone therapy throughout trial participation, and not engage in other CBTp or formalized psychosocial interventions concurrently with the study intervention.

### Participant Compliance

Being administered by professionals (and not self-administered), it is easy to appreciate the compliance with the intervention. The Personal Evaluation of Transitions in Treatment (PETiT) questionnaire assesses compliance with medication. Even if the participant agrees to participate in this study, they must continue to take their current pharmacological treatment.

Participants who are unable to follow instructions given to them about the study may be temporarily suspended or withdrawn from the study.

### Other Participant Care Considerations

The primary standard of care is medication management for adults with schizophrenia. When an individual requires other services or care, generally a referral is made to obtain these services. A proportion of adults with schizophrenia in the community may also have social or skill support via a community treatment team. The research laboratory is situated in a hospital setting, which is well resourced to support care in case of an emergency on-site. Participants will be receiving their standard, usual care throughout the study.

### Efficacy Assessments/Measurement of Effect

Therapeutic improvement, in our study, was defined as expected by statistically significant changes in some of our primary as well as secondary outcomes. To capture the progress in clinical improvement, we chose 2 validated scales that show high reliability and sensitivity to schizophrenia symptomatology—the PANSS and the NSA. The CFS was added as an additional measure for the executive function. We considered participants to be good responders to the intervention if there was an increase in PANSS General Scores higher than or equal to 20% of their baseline scores at the end of the intervention, with an improvement in scores of the PANSS Positive and PANSS Negative scales of at least 15% compared with the baseline. The therapeutic improvement also included a 20% decrease in scores for the NSA scale and a 20% increase in CFS scores at the end of the intervention, compared to baseline.

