### Objectives

This study compares the effects of a harmless, low-voltage electrical stimulation (tACS) with placebo stimulation (sham tACS) applied for 20 minutes at the beginning of the CBTp session to increase the efficacy of psychotherapy in people living with schizophrenia.

Primary objectives are to determine whether (1) the new intervention protocol using tACS will enhance the EEG activity, expecting that CBTp will enhance EEG activity in clients with schizophrenia at the end of therapy for both groups, with a better outcome for the group with active tACS stimulation; and (2) tACS applied at the beginning of the CBTp sessions in people with schizophrenia will predict better responses to therapy (compared with the sham tACS/CBTp). CBTp is expected to improve the scores of the PANSS, NSA-16, and Cognitive Flexibility Scale (CFS).

The secondary objectives are to determine whether (1) there will be an improvement of level of functioning and quality of life in both intervention groups, with a superior outcome for the group receiving tACS intervention (psychological and psychosocial tests); (2) higher in-session HRV predicts a better response to CBTp (the expectation is that baseline HRV will predict symptom improvement and increase over the course of therapy); and (3) the response to tACS/CBTp intervention is gender specific; considering that cognitive and emotional status is gender dependent, we expect that the therapeutic response could be gender specific.

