### Statistical Considerations: Sample Size

This is a pilot randomized study with 28 participants (14 per arm). The primary goals are to evaluate recruitment feasibility, acceptability, and safety, and to produce unbiased estimates of the standard deviation and preliminary effect sizes of the primary outcome to inform sample-size calculation for a future definitive trial [31]. A target of 28 participants is consistent with common pilot rules-of-thumb (approximately 12-20 per arm) and provides sufficient precision to estimate recruitment and retention rates and the outcome variance. This pilot is not powered for hypothesis testing of efficacy (with n=14 per group, the minimal detectable standardized effect is large, ~*d*=1.1); outcome analyses will therefore be descriptive and will report effect estimates with 95% CIs as inputs for future sample-size calculations. To allow for expected attrition (approximately 15%-20%), we will recruit up to 33-40 participants. The generalizability of our findings is limited by the small sample size (n=28) and recruitment from a single treatment site. Patients in this cohort may differ from the broader schizophrenia population with respect to illness chronicity, symptom severity, comorbid psychiatric or medical conditions, and sociodemographic characteristics. In addition, the specialized treatment context may not reflect the experiences of individuals receiving care in community or primary care settings, where clinical resources and treatment approaches may vary. These factors restrict the extent to which the present results can be applied to other patient populations. Replication in larger, multisite, and more heterogeneous cohorts will be essential to establish the robustness and external validity of the findings.

The statistical analysis plan will use SPSS (version 29, IBM Corp) for the main tests, including effect size (Cohen *d*) and a 95% CI: repeated measures, mixed design analysis of variance, and *t* tests for two-group comparisons. Sex and gender differences will be examined using regression models that include biological sex, BSRI masculinity and femininity scores, and their interaction terms, with exploratory subgroup analyses based on BSRI classifications.

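### Therapeutic improvement is defined by significance in an unstated selection of outcomes, which contradicts the protocol's own statement that outcome analyses are descriptive

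*Protocol article*

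**What the plan says.** Three parts of the protocol article bear on this point.

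- **Efficacy Assessments/Measurement of Effect.** Therapeutic improvement is "defined as expected by statistically significant changes in some of our primary as well as secondary outcomes". The same section then gives percentage thresholds for the PANSS scales, the NSA and the CFS, all relative to the participant's own baseline.
- **Statistical Considerations: Sample Size.** "The primary goals are to evaluate recruitment feasibility, acceptability, and safety", together with estimating the standard deviation and preliminary effect sizes. "This pilot is not powered for hypothesis testing of efficacy", because "with n=14 per group, the minimal detectable standardized effect is large" (d about 1.1), and "outcome analyses will therefore be descriptive and will report effect estimates with 95% CIs as inputs for future sample-size calculations". The section also names repeated-measures and mixed-design ANOVA and two-group t tests.
- **Objectives.** The first primary objective is worded as "expecting that CBTp will enhance EEG activity in clients with schizophrenia at the end of therapy for both groups", with a better result hoped for under active tACS. CBTp is also expected to improve PANSS, NSA-16 and CFS scores. The abstract's conclusions repeat the expectation for both groups.

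The CBTp Intervention section and Table 1 give both arms the same CBTp. The randomized difference is active versus sham tACS.

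**The concern.** The efficacy section and the sample-size section cannot both govern the same data. One makes significance the mark of improvement. The other says the trial is not built for such tests and will report estimates with intervals.

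The significance rule is also open-ended. The word *some* fixes neither the number nor the identity of the outcomes, and the sentence does not name the contrast. Only participants are blinded (Enrollment and Randomization), so any later choice of outcomes would be made by staff who know the allocation. What is at stake is what the trial may claim at its end.

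The attribution to CBTp is a smaller, separate matter. With CBTp in both arms, change shared by the arms cannot be told apart from the passage of time, practice on the tests, usual care or regression to the mean.

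**Working it through.** **Inputs.** The design has 14 per arm. There are four primary outcomes: EEG, PANSS, NSA-16 and CFS. Seven secondary outcomes are measured more than once: HRV, WHODAS 2.0, Q-LES-Q-SF, PSS, PETiT, WAI-SR and Stroop. The Brief Betrayal Trauma Survey and BSRI are taken once only. That gives 4 + 7 = 11 outcomes. The article states neither alpha nor power. Two-sided 0.05 (consistent with its 95% CIs) and 80% power are assumed. Correlations between outcomes are not given, so a range is shown.

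**1. The plan's own figure.** For a two-sample t test with 26 df and noncentrality d × √(14/2), 80% power needs d = 1.100. The normal approximation gives (1.960 + 0.842) × √(2/14) = 1.059. The stated value of about 1.1 is reproduced. Power at smaller effects:

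| True d | Power, 14 per arm |
|---|---|
| 0.3 | 11.9% |
| 0.5 | 24.7% |
| 0.8 | 53.1% |

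The sample-size section is therefore right that the pilot cannot test efficacy.

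**2. False-positive chance if one significant outcome is enough.** This assumes one between-arm test per outcome and no true effect. With independent outcomes it is 1 − 0.95^k. The correlated columns come from 20,000 simulated trials each, with equal pairwise correlation.

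| Outcomes k | Independent | r = 0.3 | r = 0.5 | r = 0.7 |
|---|---|---|---|---|
| 4 primary | 18.5% | 17.4% | 15.4% | 13.4% |
| 11 repeated | 43.1% | 37.4% | 31.0% | 22.7% |

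**3. If at least two are needed.** Over 11 outcomes the chance is 10.2% when independent and 11.3-12.1% at correlations of 0.3 to 0.7. Over the 4 primary outcomes alone it is 1.4% when independent and 2.3-4.7% when correlated.

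**4. Upper bound.** Testing each PANSS subscale and each visit separately gives 3 × 3 (PANSS) + 3 (NSA-16) + 4 (CFS) + 1 (EEG) = 17 tests, and 1 − 0.95^17 = 58.2%. At correlation 0.5 this falls to about 39%, and at 0.7 to about 28%.

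**5. If change from baseline counts.** For a paired t test the noncentrality is d × √n, where d is the mean change divided by the SD of the change. Let both arms change equally, so that the tACS effect is zero.

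| Change, in SDs of the change | One arm, n = 14 | Both arms pooled, n = 28 |
|---|---|---|
| 0.5 | 41.0% | 72.3% |
| 0.8 | 79.0% | 98.3% |

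A between-arm effect of 0.5 has 24.7% power. The definition is thus easier to meet on the contrast that says nothing about tACS.

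**The case against.** The strongest reply is that the sample-size section already takes the correct position, so this is one stray sentence in a declared pilot. That limits the repair to wording, but it does not remove the conflict: the stray sentence is the one that defines improvement. A separate analysis plan would not settle it either, since the objection is to what the article states and not to what it leaves out.

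Other replies carry weight:

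- **Change from baseline.** A reader might infer that *changes* must mean pre-post change. The sentence does not say so. The article plans mixed-design ANOVA, two-group t tests and between-subject EEG comparisons, so a between-arm reading is open. Only the percentage thresholds are explicitly against baseline.
- **The tACS contrast.** A reader might infer that any claim would say nothing about tACS. The Objectives do ask for a better outcome than sham, and that valid comparison is planned.
- **The count of 17.** The planned mixed ANOVA can give one test per outcome, so 58% is an extreme and not the expected figure.
- **The thresholds.** They do name scales and a time point. However, they classify participants, and they cover neither EEG nor any secondary outcome, so they do not say which significant results count.
- **More than one outcome.** The plural may imply at least two. Confined to the 4 primary outcomes, that keeps the chance under 5%, but the sentence includes secondary outcomes, where it is 10-12%.
- **CBTp.** The attribution is phrased as an expectation, not an analysis rule, and stands outside the definition.

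**Conclusion.** The contradiction is on the page and needs correcting. Followed literally, the definition permits an improvement claim with no true effect in about 13-19% of trials over the 4 primary outcomes and 23-43% over 11, if one significant between-arm result suffices. The ceiling is 58% if every subscale and visit is tested separately. On a from-baseline reading, a shared change of 0.5 SD is significant in about 41% of arms of 14 with no tACS effect. These figures rest on unadjusted two-sided 0.05 tests, 14 analysed per arm, the outcome count above and the stated correlations.

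The attribution of shared change to CBTp also needs rewording, as a lesser point.

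Two further readings go too far. A reader might infer that the trial can hardly fail to claim improvement, but 13-58% is not near certainty. A reader might also infer that the next trial will be sized on this pilot's point estimate. The article only offers the estimates and their CIs as inputs.

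**What to change.** 1. In Efficacy Assessments/Measurement of Effect, delete the sentence that defines improvement by statistical significance.
2. State there, in line with the sample-size section, that the effect of interest for each outcome is the active-minus-sham difference with its 95% CI, and that no efficacy claim will be made from p-values.
3. In the Objectives and the abstract's conclusions, describe change seen in both groups without crediting it to CBTp.

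The cost is wording only: no change to sample size, visits, assessments or treatment. The downside is that the trial gives up claiming efficacy from selected significant results.

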**Methods:**

This is a pilot, prospective, randomized, repeated-measures, single-blind study design. We expect to enroll 28 participants randomly assigned to one of two treatment arms: arm 1 (tACS/CBTp, n=14) or arm 2 (sham tACS/CBTp, n=14; tACS is sham, but CBTp is active). The intervention with active or sham tACS/CBTp will take place weekly for 16 weeks. Primary outcome measures—electroencephalogram, Positive and Negative Syndrome Scale, 16-item Negative Symptom Assessment, and Cognitive Flexibility Scale—will evaluate the efficacy of treatment at the end of the intervention and at the two follow-ups. We will use SPSS (version 29, IBM Corp); the main tests will include repeated measures and mixed design ANOVA.

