tACS, the focus of our study, applies a low-intensity sinusoidal electrical current to the brain through electrodes placed on the scalp, and it is thought to boost the brain’s own oscillation by way of entrainment. When a single frequency is applied, this exogenous oscillation will synchronize with the brain’s endogenous frequency. Conversely, multiple frequencies lead to desynchronization of cortical oscillations [24]. The value of the frequency applied thus becomes a determining factor in the effects sought and identified in tACS studies.

Research focusing on tACS mechanisms has shown that effects result from manipulating the membrane potential of neurons that are aligned with the introduced electric field, mostly pyramidal cells in layer V [25,26]. Upon stimulation by tACS, which will cause an alternating change in membrane potential, these cells demonstrate a resonance specific to the frequency of stimulation, with long-term aftereffects—70 minutes after one stimulation session for 20 minutes [19]—and implications on oscillatory cortical connectivity between different cortical regions [27]. In auditory hallucinations, research has demonstrated interhemispheric miscommunication, where tACS can manipulate auditory perception in healthy participants by decoupling this interhemispheric connectivity [28]. The advantage of using tACS over other noninvasive brain stimulation modalities lies in its effectiveness in entraining endogenous brain oscillations, as it mimics the alternating nature of these oscillations [29,30].

From a practical standpoint, tACS exhibits superior cost, portability, tolerability, and safety profiles [17]. tACS is a feasible tool that reshapes or resynchronizes intrinsic brain rhythms, manipulating the associated brain functions without adding extra excitatory or inhibitory burden.

We hypothesize that tACS targeting gamma oscillations, added to each CBTp session, will improve cognitive performance in individuals living with schizophrenia under their usual antipsychotic medication by restoring neural synchrony and enhancing cortical connectivity. This will subsequently improve clinical and functional status and medication adherence.

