The NSA-16 assesses the presence, severity, and range of negative symptoms associated with schizophrenia [33]. For rapid clinical assessment or screening of patients for negative symptoms, the NSA-4 was developed as a simplified version, retaining only 4 of the 16 items: restricted speech quantity, reduced emotion, reduced social drive, and reduced interests. Each of the 4 items and the overall global negative symptoms is rated on a 1- to 6-point scale, where “1” represents no reduction from normal behaviors associated with the item and “6” represents a severe reduction in or absence of the behavior, with markedly impaired functionality. With respect to overall accuracy and predictive validity, the NSA-4 is comparable to the NSA-16. [Time frame: NSA-16 will be applied at visit 2, baseline (week 1); visit 4, end of intervention (week 17); visit 5, follow-up 1 (week 21); and visit 6, follow-up 2 (week 29).]

The CFS assesses cognitive flexibility as a factor that facilitates the individual’s adaptability toward events [34]. Cognitive flexibility refers to a person’s awareness of the existence of different communication styles in every situation, as well as their willingness and self-efficacy to employ these styles. The scale has 12 items pertaining to the 3 elements of cognitive flexibility: a person’s awareness of alternative communicative styles, willingness to be communicatively flexible, and self-efficacy in being communicatively flexible. The scale uses a 6-point Likert-type scale for each item (with 6 as “strongly agree,” 5 as “agree,” 4 as “slightly agree,” 3 as “slightly disagree,” 2 as “disagree,” and 1 as “strongly disagree”). The total score was used to calculate a global score ranging from 12 to 72, with questions 2, 9, 11, and 12 being reverse-coded. A higher score indicates higher cognitive flexibility. [Time frame: CFS will be applied at visit 2, baseline (week 1); visit 3, midpoint of intervention (week 9); visit 4, end of intervention (week 17); visit 5, follow-up 1 (week 21); and visit 6, follow-up 2 (week 29).]

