The Stroop Color and Word Test (hereafter just Stroop test), developed by John Ridley Stroop, is a neuropsychological test that measures cognitive interference by asking participants to name the ink color of words, which are printed in a color that conflicts with the word itself. The Stroop scores are based on 3 factors—color naming, interference, and speed—and converted into a *T*-score for interpretation. A *T*-score of 40 or less is considered low, while a score above 40 is considered normal. [Time frame: The Stroop test will be applied at visit 2, baseline (week 0); at visit 4, end of intervention (week 17); and at the 2 follow-ups (week 21 and week 29).]

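### The Cognitive Flexibility Scale is labelled a measure of executive function, but it is a questionnaire about communication, and no primary outcome tests the hypothesised gain in cognitive performance

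*Protocol article*

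**What the plan says.** The hypothesis that closes Background and Scientific Rationale is that gamma tACS added to each CBTp session "will improve cognitive performance in individuals living with schizophrenia under their usual antipsychotic medication". Clinical and functional gains are expected to follow from that.

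The Abstract's Methods list the primary outcomes as EEG, PANSS, "16-item Negative Symptom Assessment, and Cognitive Flexibility Scale". Efficacy Assessments/Measurement of Effect gives the last of these its role: "The CFS was added as an additional measure for the executive function". The same section includes in therapeutic improvement "a 20% increase in CFS scores at the end of the intervention, compared to baseline".

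Primary Outcome Measures then describes the scale. Cognitive flexibility is a person's "awareness of the existence of different communication styles in every situation", together with willingness and confidence to use those styles. Two of the three elements are "willingness to be communicatively flexible, and self-efficacy in being communicatively flexible". On format: "The scale uses a 6-point Likert-type scale for each item", with 12 items and a total from 12 to 72.

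The Stroop appears under Secondary Outcome Measures, where it "is a neuropsychological test that measures cognitive interference by asking participants to name the ink color of words". Table 2 schedules it at visits 2, 4, 5 and 6.

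**The concern.** The label and the description do not match. Executive function is something a person does under test. The CFS, as described, records what a person believes about his or her own communication. The shared name makes the slip easy to miss: the rationale and the EEG paragraph use cognitive flexibility for a function of frontal networks and prefrontal gamma, while the scale uses it for attitudes to communicating.

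Two errors of interpretation become possible.

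- The CFS could rise because a talking therapy has changed beliefs and confidence, and be reported as better executive function. The Objectives section itself expects CBTp to improve the CFS.
- Stimulation could improve executive control and leave the CFS unchanged, and this would be read as no cognitive effect.

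The pilot is also meant to supply standard deviations and preliminary effect sizes for a definitive trial. If the CFS is taken as the cognitive measure, it will be the natural candidate for that planning.

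**Working it through.** **The plan's own figure.** Statistical Considerations: Sample Size gives a minimal detectable effect of about d = 1.1 with 14 per arm. Alpha and power are not stated. Assuming a two-sided alpha of 0.05 and 80% power:

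- Two-sample t test (noncentral t): d = 1.100.
- Normal approximation: (1.96 + 0.842) × √(2/14) = 1.06.

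The figure is reproduced. It is a standardised effect at 14 per arm, so it is the same for the CFS and the Stroop. The point concerns what is measured, not power.

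**What each primary outcome measures, from the article's own text.**

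| Primary outcome | Described as | Performance test of cognition? |
|---|---|---|
| EEG gamma | Physiological biomarker linked to cognition | No |
| PANSS | Clinician-rated symptoms | No |
| NSA-16 | Negative symptom ratings | No |
| CFS | Agree/disagree items on communication | No |

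The count is 0 of 4. Of the remaining instruments, the MoCA is used only to screen people over 65. The Stroop is the only performance test of cognition used as an outcome.

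**What the CFS threshold requires.** 12 items scored 1 to 6 give 12 × 1 = 12 to 12 × 6 = 72, as the article states. A 20% rise needs 0.20 × baseline points. The article gives no baseline mean, so I assume a range:

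- Baseline 40: 8 points.
- Baseline 50: 10 points.
- Baseline 60: 12 points, which reaches the ceiling of 72 (72 / 1.2 = 60).

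If each answer shifts by one category, 8 to 12 of the 12 answers have to move. The criterion can be met entirely by changed agreement with statements, with no change in any task.

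**Does the arm comparison remove the problem?** Only in part. Both arms receive the same CBTp, so its shared effect cancels in the between-arm contrast. The 20% criterion, however, is a within-person change from baseline, and there the CBTp effect does not cancel. Between arms, the Abstract's Objective says tACS is meant to raise therapeutic engagement. More engagement could raise confidence in communicating, and so the CFS, without any change in executive function.

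**Stroop timing.** Secondary Outcome Measures places the visit 2 baseline at week 0. Table 2 places visit 2 at week 1.

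**The case against.** The strongest case on the other side has five parts.

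1. EEG gamma is the first primary outcome and is tied in the text to working memory, flexibility and attention control. A reader might infer that the CFS carries the whole cognitive claim. The document does not support that: the CFS is called only an additional measure. This stands, but EEG gamma is still not a test of performance.
2. A reader might infer that the Stroop lies outside the definition of therapeutic improvement. It does not. The definition opens with significant change in some primary and secondary outcomes, and the Stroop is a secondary outcome. What it lacks is a named role or threshold.
3. The numbered primary objectives speak of EEG activity and response to therapy, not of cognitive performance, and a CFS rise in both arms is what the protocol predicts. True, but the hypothesis and the executive-function label are also in the document, and they lead to the misreading.
4. The pilot is declared unpowered for efficacy, its outcome analyses are descriptive, and the Stroop SD will be available anyway. So it cannot be said that the main trial would be planned on the wrong construct; no passage says it will be sized on the CFS. This softens the consequence, but a descriptive estimate under the wrong label still misinforms.
5. Replacing the CFS by the Stroop as a primary is tempting, but the text does not require it. By November 1, 2025, 15 participants were enrolled, and only participants are blinded. A swap now would invite a charge of outcome switching. The Stroop also covers interference, color naming and speed, not memory. This objection stands in full, and the swap is not recommended.

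**Conclusion.** The concern holds in a limited form. The executive-function label is contradicted by the article's own account of the CFS, and 0 of 4 primary outcomes measures the cognitive performance that the hypothesis names. The one outcome that does so is already collected at four visits but has no designated role.

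The consequence is one of interpretation: a CFS change could be reported as a cognitive change. No figure in the plan is wrong on this account, and the detectable effect stays at about d = 1.1.

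The verdict rests on one inference, that the CFS is self-rated. The article does not say so outright; it follows from the agree/disagree format and the self-efficacy content.

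**What to change.** Keep the four registered primary outcomes, and make these changes in one dated amendment.

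- **Efficacy Assessments/Measurement of Effect:** describe the CFS as questionnaire-based cognitive or communication flexibility, and remove the reference to executive function. State that a CFS change alone will not be reported as a change in cognitive performance or executive function.
- **Objectives and Secondary Outcome Measures:** name the Stroop, visit 4 (week 17) against the visit 2 baseline, compared between arms with a 95% CI, as the key secondary outcome testing the cognitive-performance hypothesis. Say which Stroop score is meant.
- **Secondary Outcome Measures and Table 2:** reconcile the Stroop baseline week (week 0 against week 1).
- **Statistical Considerations: Sample Size:** state that the Stroop SD and effect size will be reported for planning the main trial.

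The amendment should precede any between-arm look at the data. This matters because Disseminations foresees a preliminary or interim analysis.

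The cost is protocol and registry wording, with no new visit, test or primary outcome. The remaining weaknesses are that the Stroop does not cover memory and has no week 9 reading.
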